## Abstract

**Background:**

FLASH therapy is a treatment technique in which radiation is delivered at ultra-high dose rates (≥ 40 Gy/s). The first-in-human FAST-01 clinical trial demonstrated the clinical feasibility of proton FLASH in the treatment of extremity bone metastases. The objectives of this investigation are to assess the toxicities of treatment and pain relief in study participants with painful thoracic bone metastases treated with FLASH radiotherapy, as well as workflow metrics in a clinical setting.

**Methods:**

This single-arm clinical trial is being conducted under an FDA investigational device exemption (IDE) approved for 10 patients with 1–3 painful bone metastases in the thorax, excluding bone metastases in the spine. Treatment will be 8 Gy in a single fraction administered at ≥ 40 Gy/s on a FLASH-enabled proton therapy system delivering a single transmission proton beam. Primary study endpoints are efficacy (pain relief) and safety. Patient questionnaires evaluating pain flare at the treatment site will be completed for 10 consecutive days post-RT. Pain response and adverse events (AEs) will be evaluated on the day of treatment and on day 7, day 15, months 1, 2, 3, 6, 9, and 12, and every 6 months thereafter. The outcomes for clinical workflow feasibility are the occurrence of any device issues as well as time on the treatment table.

**Discussion:**

This prospective clinical trial will provide clinical data for evaluating the efficacy and safety of proton FLASH for palliation of bony metastases in the thorax. Positive findings will support the further exploration of FLASH radiation for other clinical indications including patient populations treated with curative intent.

**Registration:**

ClinicalTrials.gov NCT05524064.

## Background

FLASH therapy is an emerging form of radiation therapy (RT) in which radiation is delivered at ultra-high dose rates of at least 40 Gy/s. Compared to RT given at conventional dose rates, FLASH RT has been shown in multiple animal models to cause less injury to normal cells and tissue, while having equal or greater tumor cell killing [1–6]. The mechanism for this protective effect of normal tissues by FLASH is thought to be related, in part, to FLASH resulting in lower levels of toxic oxygen-reactive species in normal tissues as compared to conventional RT [7]​.

There has been one published case report of the use of electron FLASH RT in a human. A single patient with cutaneous T cell lymphoma and extensive prior RT to the skin was treated with a 15 Gy single fraction using electron FLASH RT for a recurrent cutaneous lymphoma lesion. This resulted in a complete response of the lesion with minimal toxicity to the surrounding skin [8]​.

FAST-01, the first prospective clinical trial of FLASH, evaluated the feasibility of proton FLASH therapy for the palliative treatment of painful bone metastases in the extremities [9]. Ten patients were enrolled and treated with an 8 Gy single fraction regimen delivered at FLASH dose rates to 12 metastatic sites. All treatments were delivered uneventfully, and study participant time on table (which includes positioning on the treatment couch, imaging, and FLASH treatment delivery) averaged 15.8 min. Reduction in pain at the treated sites was consistent with published literature using a single 8 Gy fraction of conventional photon RT (RTOG 9714). The overall pain response rate to FLASH treatment at 3 months was 66.7% (50% complete response: 6/12 treated sites, 16.7% partial response: 2 treated sites). In follow-up, 16.73% (2 of 12) of the FLASH treatment sites required additional treatment. Treatment was well tolerated. There were 23 serious adverse events (SAEs) reported with 22 scored as definitely not related and 1 scored as probably not related to the FLASH treatment. Similar to the prior RTOG 9714 trial, acute, mild grade 1 hyperpigmentation in the FLASH study participants was observed, with 4/10 participants affected compared to 16/433 (15-grade 1 and 1-grade 2) skin AEs in RTOG 9714 [10]. The AEs affecting skin are consistent with known side effects of radiation treatment and no unexpected AEs were reported. The results of the FAST-01 pilot study confirm the feasibility of FLASH radiation treatment in a routine clinical setting and support the further exploration of FLASH radiation treatment for other clinical indications [11].

A long-term goal of future clinical trials is to evaluate FLASH RT for the potentially curative treatment of patients with thoracic malignancies. The novel FAST-02 clinical trial, described in this protocol, builds on the FAST-01 experience and is the next step in further assessing the safety and efficacy of FLASH RT in different anatomic sites. FAST-02 was designed to evaluate the safety profile of FLASH RT in lower-risk thoracic clinical presentations as well as the pain response associated with a palliative FLASH RT regimen prior to treating more complex clinical presentations with curative intent.

Patients with painful bone metastases continue to represent an ideal population for a feasibility study of FLASH therapy, because the palliative effects of standard of care RT using single-dose radiation regimens are well understood [11–14]. It is expected that the participants of this study will receive the same pain control benefits as if treated with conventional dose rate photon RT. Normal tissue toxicity is expected to be mild.

## Methods

### Objectives

The objectives of this clinical trial are.

To assess toxicities of FLASH treatment (co-primary objective).To assess FLASH efficacy as pain relief at the treated site(s) (co-primary objective).To assess workflow metrics of FLASH RT to the thorax in a clinical setting (secondary objective).

### Study design

In this prospective clinical trial, 10 study participants will undergo FLASH therapy with palliative intent to 1–3 painful bony metastases in eligible treatment sites in the thorax (e.g., ribs, clavicle, scapula, and sternum, but not the spine). As this is an exploratory study, the sample size was approved by the FDA as sufficient to address the objectives. Study activities will take place at the Cincinnati Children’s Hospital Medical Center (CCHMC) Proton Therapy Center with IRB approval and under an FDA Investigational Device Exemption (IDE). The Cincinnati Cancer and Blood Disease Institute Data Safety Monitoring Board (DSMB) will serve as the DSMB for the study.

Patients who meet the initial eligibility requirements and provide informed consent will be enrolled in the study. Study duration includes radiation treatment simulation, radiation treatment planning, treatment delivery (≤ 10 business days from treatment simulation), and post-treatment follow-up. Participants will continue follow-up activities until they withdraw from the trial or their health precludes further participation.

### Study population

Patients will be informed about the study primarily by radiation oncologists and their staff. Patients eligible to enroll are adults undergoing palliative RT for metastases in bones of the thorax, excluding the spine, who meet all of the inclusion criteria and do not meet any of the exclusion criteria.

In addition to the metastatic sites to be treated with FLASH therapy patients may have other bone metastases that may be treated with conventional RT. In the case that there is more than one lesion treated, no overlap of FLASH radiation fields with other FLASH or conventional radiation fields is allowed.

The initial screening process will assess the initial inclusion criteria. After providing informed consent, study participants will undergo CT simulation imaging for the purpose of treatment planning. The treatment planning process will allow assessment of the final inclusion criterion, i.e., whether a clinically acceptable FLASH treatment plan can be designed for their lesion(s).

Participants in this clinical trial may also be enrolled in other studies, provided that those studies do not have an impact on the primary endpoints of this trial. Steroid medication for the treatment of bone pain is optional and at the discretion of the prescribing physician as needed.

### Initial inclusion criteria

Patient age ≥ 18 years.1–3 painful bone metastasis(-es) requiring treatment in the ribs, clavicles, scapulae, or sternum; if more than 1 metastasis can be treated within the same treatment field, it will be counted as 1 metastatic site for the purpose of trial treatment.Bone metastases that can be treated within a field size up to 7.5 cm x 30 cm without overlap of other radiation fields.Life expectancy > 6 months (in the judgment of the investigator).Patients who are able to comply with the protocol.Provision of signed and dated informed consent form.

### Final inclusion criteria

A clinically acceptable FLASH treatment plan.

### Exclusion criteria

> 3 painful bone metastases of the thorax requiring palliative RT. If > 1 metastasis can be treated within the same treatment field, it will be counted as one metastatic site for the purpose of trial treatment; patients with > 3 painful bone metastases in the thorax requiring treatment are more likely to have generalized thoracic pain that may confound measurement of pain relief response to treatment.Overlap of FLASH radiation fields with any previous or planned radiation fields to the same site.Patients with pathologic bone fractures in the treatment field.Patients with metal implants in the treatment field (proton range and dosimetry are less certain in the presence of metal).Patients with symptomatic pneumonitis at the time of screening, or a history of symptomatic radiation pneumonitis.Patients with known contraindications to thoracic radiation.Patients who received or will receive cytotoxic chemotherapy and/or any prescribed systemic therapy known to impact tissue response to radiation within 2 weeks prior or 1 week following their planned radiation treatment (concurrent therapies may affect the tissue response to radiation).Prior local therapy modality to the treatment site(s) within 2 weeks of study enrollment that, in the judgment of the investigator, might compromise interpretation of pain response.Patients with persistent toxicity ( except for alopecia and peripheral neuropathy) grade > 1 from prior systemic therapy that is within the proposed treatment field.Patients with pacemakers or other implanted devices at risk of malfunction during RT.Patients with any other medical condition or laboratory value that would, at the discretion of the investigator, preclude the patient from participating in this clinical investigation.Patients at known risk of enhanced normal tissue sensitivity to RT due to inherited predisposition or documented comorbidity that might lead to hypersensitivity to ionizing radiation.Patients enrolled in any other clinical studies that the investigator believes to conflict with this clinical investigation.Patients who are pregnant or nursing.

## Intervention

### CT simulation and planning target volume (PTV)

Simulation imaging will be performed as part of the standard of care in order to develop the radiation treatment plan. During the simulation procedure, the subject will be placed on the CT simulator couch in a stable and reproducible position suitable for targeting the metastatic lesion(s). Immobilization devices such as a Vac-LokTM bag (CIVCO Radiotherapy, Coralville, Iowa), are recommended to aid in immobilizing the target site(s) and for reproducing the subject’s positioning at the time of treatment. The CT imaging will be obtained through the areas of interest and used for RT planning.

Patients will undergo respiratory 4DCT imaging unless a 4DCT is not clinically feasible in the judgment of the treating investigator (see below). The 4DCT scan will be acquired under conditions of free breathing to assess the extent of target motion.

If the maximum target excursion is > 10 mm, an abdominal compression approach will be used to reduce the extent of motion. An additional 4DCT scan of the subject with abdominal compression will then be acquired and used for treatment planning in combination with an Internal Target Volume (ITV) approach due to residual target motion.If the subject’s motion cannot be reduced to less than 10 mm, the subject will be withdrawn from the study and replaced.If the maximum target excursion is ≤ 10 mm, the existing 4DCT scan will be used for treatment planning (using an ITV approach). No additional motion mitigation strategies (beyond the ITV approach used in planning) are required.

Where a 4DCT is not clinically feasible, a conventional simulation CT scan with the subject in free-breathing will be acquired and used for treatment planning.

Women of childbearing age must have a negative urine or serum pregnancy test prior to CT simulation. If the pregnancy test is positive, the subject will be removed from the study and replaced.

### Treatment planning

The simulation CT images will be electronically transferred to the Eclipse Treatment Planning System v16.5 (Varian Medical Systems, Palo Alto), as per the standard clinical workflow.

For an ITV planning approach based on the 4DCT, the target(s) will be delineated by one of the radiation oncologist investigators who will designate the Gross Tumor Volume/Clinical Target Volume (GTV/CTV). The ITV will be created based on the target (GTV/CTV) locations on the inhale and exhale phases corresponding to the maximum extent of target motion and will be propagated to the average CT dataset for treatment planning and dose calculation. A Planning Target Volume (PTV) margin of ≥ 5 mm will be added to the ITV, to account for set-up uncertainty.

Where a 4DCT is not acquired, the target(s) will be delineated by one of the radiation oncologist investigators on the helical CT scan, who will designate the GTV/CTV. A PTV margin of ≥ 5 mm will be added to the GTV/CTV, to account for set-up uncertainty and possible motion due to respiration.

Targets must be suitable for treatment within a maximum field size of 7.5 cm x 30 cm. If this is not possible, the study participant does not meet the final inclusion criterion and will be removed from the study and will not count towards the final enrollment goal of 10 treated study participants.

A single, 250 MeV transmission proton field will be used for planning. In order to ensure acceptable coverage and minimize dose to surrounding normal tissues, gantry angle, couch angle, field size and field shape (within the field tolerance) shall be appropriately selected. Consideration of beam angles that minimize impact of motion should also be made where possible.

Since the treatment will be delivered with transmission FLASH, there will be no Bragg Peak inside the body. The relative biological effectiveness (RBE) of 1.0 will therefore apply to the transmission FLASH treatment since no correction is required for Bragg Peak.

A dose of 8 Gy in a single fraction will be prescribed to the PTV at a dose rate ≥ 40 Gy/s. This dose regimen is a standard dose and fractionation for painful bone metastases, whose efficacy has been validated in prior multi-institutional prospective randomized clinical trials [15, 16].

The volume of PTV receiving 90% of the prescribed dose shall be greater than or equal to 90%, and the dose to 10% of the PTV will not exceed 110%.

There are no published dose constraints for OARs for palliative 8 Gy RT regimens, likely since historical rates of toxicities from this low-dose palliative regimen are low. However, to be conservative, relevant maximum dose limits to a point or volume for the spinal cord, esophagus and heart, and volumetric dose constraints for the lung will be followed and are presented in Table 1 (below). Given the thoracic sites of bone metastases eligible for treatment, the expectation is that there may be some lung in the radiation field. In addition, though patients with spinal metastases in the thoracic spine are not eligible for this study, the dose limit for the spinal cord was added due to the potential for out-of-field or exit dose contribution to the spinal cord, which should be low. Dose constraints are from the recommendations in the report of AAPM Task Group 101 for single fraction stereotactic body RT [17].

**Table 1 Tab1:** Normal tissue dose contraints

Tissue	Volume	Volume Max (Gy)	Max point dose (Gy)	Potential Adverse Outcome (≥ Grade 3) per TG101
Spinal Cord	< 1.2 cc	7	14	Myelitis
Lung (Right and Left)	1500 cc	7	NA-Parallel tissue	Basic Lung Function
Lung (Right and Left)	1000 cc	7.4	NA-Parallel tissue	Pneumonitis
Lung (Right and Left)	37%	8	NA-Parallel tissue	Pneumonitis
Heart/pericardium	15 cc	16	22	Pericarditis
Esophagus	5 cc	11.9	15.4	Stenosis/fistula

If more than 1 lesion is eligible for treatment with FLASH RT, the normal tissue dose limits will apply to the composite (sum) plan of all lesions treated.

The investigator will determine if the treatment plan is clinically acceptable.

A treatment plan that exceeds the dose limits in Table 1 will not be allowed. Subjects for whom clinically acceptable treatment plans cannot be created will not continue on the study (and will not undergo FLASH RT treatment) and will be replaced. The investigator will verbally communicate this to the subject, assist in making alternative arrangements for treatment, and document it on an end-of-study form.

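### With one FLASH-eligible lesion and a conventional course to another thoracic lesion, the rule that sums dose for Table 1 is not triggered, so the two courses' lung volumes need not be added

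*Protocol article*

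**What the plan says.** All references are to the protocol article.

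- **Binding limits.** Treatment planning, below Table 1: "A treatment plan that exceeds the dose limits in Table 1 will not be allowed".
- **When plans are summed.** Same section: "If more than 1 lesion is eligible for treatment with FLASH RT, the normal tissue dose limits will apply to the composite (sum) plan". The sentence goes on to define the sum as the "composite (sum) plan of all lesions treated".
- **Conventional radiotherapy alongside FLASH.** Study population: "patients may have other bone metastases that may be treated with conventional RT". The thorax is not excepted.
- **Separation of fields.** Study population: "no overlap of FLASH radiation fields with other FLASH or conventional radiation fields is allowed". Exclusion criteria, to the same effect: "Overlap of FLASH radiation fields with any previous or planned radiation fields to the same site".
- **Fracture and metal.** Exclusion criteria: "Patients with pathologic bone fractures in the treatment field". Metal implants are likewise excluded only within the treatment field.
- **Lung rows of Table 1 (right and left lung).** 1500 cc at 7 Gy, 1000 cc at 7.4 Gy and 37% at 8 Gy, with no point limit.

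**The concern.** The duty to sum depends on how many lesions are eligible for FLASH, not on how many thoracic courses the participant receives. Two FLASH courses are summed. One FLASH course plus one conventional course through the same lungs is not, if the second lesion cannot have FLASH.

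Toxicity is a co-primary objective, and Table 1 is the fixed organ-dose safeguard behind it. If total lung exposure can go beyond a row without the check registering it, the safeguard is weaker than it appears for those participants. Sample size, error rates and analysis are unaffected.

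**Working it through.** The plan gives no statistical figure here to reproduce. The check is a reading of the rules, followed by an illustration of scale.

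**1. Can the situation arise?** Take one rib lesion suitable for FLASH and a second, painful rib lesion with a pathologic fracture or metal in its own field. The second cannot have FLASH. The participant is not excluded, because those criteria concern the treatment field. The Exclusion criteria allow at most 3 painful thoracic sites requiring radiotherapy, so one FLASH site leaves 3 - 1 = 2 at most for conventional treatment.

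**2. Is the sum rule triggered?**

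| Lesions | Trigger met? | What is checked against Table 1 |
|---|---|---|
| Two FLASH-eligible, both given FLASH | Yes | Sum of both |
| Two or more FLASH-eligible, another lesion conventional | Yes | Sum of all lesions treated; may include the conventional one |
| One FLASH-eligible, another thoracic lesion conventional | No | FLASH plan alone |

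The gap is certain only in the last row.

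**3. Does non-overlap cover it?** No. FLASH fields may not overlap one another either, yet the protocol sums them. Two separate fields irradiate two separate volumes of lung, and a volumetric limit counts both.

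**4. Scale, as illustration only.**

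- From the document: field width 7.5 cm; 8 Gy FLASH prescription; the 1000 cc, 1500 cc and 37% rows.
- Assumed: two equal fields; lengths of 5, 10 or 15 cm; about 8 Gy along the whole lung path of each; total lung 3000-4000 cc. The conventional dose, technique and field size are not given.

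Lung path at which a row is reached = volume / area for one field, or volume / (2 x area) for two. Areas: 7.5 x 5 = 37.5, 7.5 x 10 = 75 and 7.5 x 15 = 112.5 cm².

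Volumes:

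- 1000 cc row read as a ceiling: 1000 cc.
- 37% row: 0.37 x 3000 = 1110 cc to 0.37 x 4000 = 1480 cc.
- 1500 cc row read as lung to be spared: 3000 - 1500 = 1500 cc to 4000 - 1500 = 2500 cc.

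| Row | 7.5 x 10, one field | 7.5 x 10, two summed | 7.5 x 5, two summed | 7.5 x 15, two summed |
|---|---|---|---|---|
| 1000 cc, ceiling | 1000/75 = 13.3 cm | 1000/150 = 6.7 cm | 1000/75 = 13.3 cm | 1000/225 = 4.4 cm |
| 37% | 1110/75 to 1480/75 = 14.8-19.7 cm | 1110/150 to 1480/150 = 7.4-9.9 cm | 14.8-19.7 cm | 1110/225 to 1480/225 = 4.9-6.6 cm |
| 1500 cc, spared | 1500/75 to 2500/75 = 20.0-33.3 cm | 1500/150 to 2500/150 = 10.0-16.7 cm | 20.0-33.3 cm | 1500/225 to 2500/225 = 6.7-11.1 cm |

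The reading of the cc rows matters. If the 1000 cc row also means lung to be spared, two 7.5 x 10 cm fields reach it at (3000 - 1000)/150 = 13.3 to (4000 - 1000)/150 = 20.0 cm instead of 6.7 cm.

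**5. Cord.** If participants with a thoracic-spine metastasis may enroll and that lesion is treated conventionally at an assumed 8 Gy, cord in that field gets about 8 Gy. That is above the 7 Gy volume limit and below the 14 Gy point limit.

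**The case against.** **The sum already covers conventional lesions.** It is defined over all lesions treated, words not confined to FLASH. This stands in part: with two or more FLASH-eligible lesions, a conventional course may well be counted. A reader might infer that conventional thoracic dose is never counted, and the text does not support that. With one FLASH-eligible lesion, however, those words do not come into play.

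**A condensed article may leave this to the full protocol.** That would answer an omission. Here the article states the rule and its trigger, and the trigger is drawn too narrowly. The full protocol may be broader; this cannot be seen.

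**Other safeguards exist.** The plan must be clinically acceptable in the investigator's judgment, and known contraindications to thoracic radiation exclude. Passing Table 1 therefore does not mean that the patient would be treated. These checks are discretionary, though, and Table 1 is meant as a fixed bar besides them. The external review of every third participant's FLASH plan comes after treatment.

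**The effect is small.** This stands. Treatment planning describes the limits as conservative for this regimen, and the baseline data in Follow-up record treatment of other bone metastases, which largely covers attribution of adverse events.

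**Spine.** Treatment planning remarks: "though patients with spinal metastases in the thoracic spine are not eligible for this study". No listed criterion excludes such a patient, so a reader might infer that an eligibility rule is missing, or even that the spine could be a FLASH target. The documents do not support either. The Abstract, Study design, Study population, Initial inclusion criteria and Discussion consistently keep the spine out as a treated site, and the remark is a subordinate clause explaining why a cord limit exists. It is most naturally loose wording.

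**Conclusion.** The point holds for one configuration: a single FLASH-eligible lesion plus a concurrent or already planned conventional course to another thoracic lesion. The protocol then requires only the FLASH plan to meet Table 1, and non-overlap does not protect the volumetric lung limits.

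Severity is minor. The documents give neither the frequency of this configuration nor the conventional dose. The path lengths rest on assumed field sizes, uniform dose, lung volume and a reading of the cc rows. They show that the gap could matter with fields of about 7.5 x 10 cm or larger and is unlikely to with 7.5 x 5 cm fields. A reader might take them, or the cord figure, as evidence of harm; they show only where a limit would be reached. The spine remark is a wording note, not a separate finding.

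**What to change.** Reword the sum rule in Treatment planning so that the Table 1 limits apply to the sum of all FLASH plans and any concurrent or already planned conventional thoracic course, including a conventional thoracic-spine course if such patients may enroll. Table 1 is built on single-fraction limits, so fractionated dose should be converted to a single-fraction equivalent by a method that the site prespecifies.

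As a wording correction, change the spine clause in the same section to say that spinal metastases are not eligible for FLASH treatment. That agrees with Study design, Study population, Initial inclusion criteria and Discussion.

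Cost: one amended sentence and one amended clause, the choice of a conversion method, a sum plan for the few participants affected, and possibly a rare screen failure. Planned fields must already be known at screening for the overlap exclusion, so little new information is needed.
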